### Sample Size

To calculate sample size, we used the calculation tool for the stepped wedge RCT design developed by Hussey et al [35]. Tang and colleagues found that in China, the proportions of MSM being told of their partners’ HIV status were 20.6% and 17.8% for most regular and casual male partners, respectively [14]. Assuming that the effect of the intervention period was superior to that of the control period, an overall growth of 10%, four intervention periods, a coefficient of variation of 0.40 (usually between 0.15 and 0.40), a two-sided α of 0.05, and 90% power, the total sample sizes of 620 and 560 for the most recent regular and casual male partners were significant. Given a loss to follow-up of 20%, we made a conservative estimate that 200 men in each group would be sufficient to detect differences between the intervention and control conditions.

### Data Management

Survey data and photographs of testing results will be collected through an online survey platform. Only researchers will have an account and password, so the safety and privacy of participants are ensured. Data will be downloaded directly and saved in an identifiable format on a computer. When the data are transmitted, some identifiable variables, such as name, telephone number, and address, will be encrypted for privacy protection. A specific telephone will be used for daily contact with participants during the trial and will be locked in a document cabinet after work every day.

### Analysis Plan

Survey data will be imported into SAS for data management and analysis. The primary outcome will be the self-reported disclosure of HIV status by sexual partners during the past 3 months. Generalized linear mixed models will be used to compare the differences between intervention and control conditions for primary outcome analysis. Intervention status and time will be treated as fixed effects, whereas group clusters and individuals will be estimated as random effects. The effects of the intervention will be reported with 95% confidence intervals and *P* values. *P*<.05 will be considered significant.

Similar methods will be used to measure secondary outcomes, including the frequency of HIV testing uptake, frequency of syphilis testing, number of sexual partners, and unprotected sex. In addition, logistic regression analysis will be used to explore the relationship between the HIVST results of sexual partners and condom use during sexual intercourse. Factors such as sexual orientation, HIV status, type of sexual partners, HIV testing-related violence, history of HIV testing, and others will be measured to examine their association with disclosure of HIV status to sexual partners.

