**Assessments**												
	Online surveys						X	X		X		X

^a^T1: 1-3 months after enrollment.

^b^T2: 3-6 months after enrollment.

^c^T3: 6-9 months after enrollment.

^d^T4: 9-12 months after enrollment.

^e^I: Intervention condition.

^f^C: Control condition.

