### Study Measures and Outcomes

Baseline and follow-up surveys will be completed via mobile telephone and collected through Gold Data, the most popular online data collection system platform in China. Study administrators will establish an online survey form and generate a QR code link to the survey questionnaire. Study subjects will scan the QR code provided and complete the survey, indicating their willingness to participate in the project and the conditions for participation. A link to the questionnaire is also included in the HIVST kit instruction manual mailed to the respondent. After completing the HIVST, participants scan the QR code and provide their identification numbers, social background, and behavioral information, and uploaded photos of self-test results.

Data privacy is assured by contractual agreement with Gold Data, as well as Gold Data’s encryption systems. Participants are asked to use pseudonyms rather than their real names. A secondary identifier is provided with each participant’s questionnaire. Study administrators also used physical controls, such as locked storage for study data, to ensure participants’ privacy and data security.

A baseline questionnaire will be used to screen candidates for inclusion eligibility. Eligible participants will be required to complete the remaining questions in the surveys. Data collection will include social background (age, level of education, monthly income, occupation, marital status, and sexual orientation), high-risk sexual behaviors, and experience of HIV testing. High-risk sexual behaviors, including the number and type of sexual partners, number of condom-less oral or anal sex encounters, and knowledge of sexual partners’ HIV status during the past 3 months, will be documented. HIV testing history, including the number of self-reported HIV tests, experience with HIVST, and variables, will also be recorded.

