Participants will be asked to complete follow-up surveys within one week after being notified via WeChat message. Follow-up surveys will be performed at 3, 6, 9, and 12 months after enrollment. The distribution of HIVST kits, sexual partners’ willingness to use the kits, and the rate of HIV status disclosure by sexual partners will be collected. In addition to high-risk sexual behaviors and HIV testing experience in the baseline survey, sexual decision making will also be measured to evaluate the effect of HIV status disclosure. Questions regarding sexual decisionmaking will focus mainly on whether to have sex and condom use (never/sometimes/usually/always using) for oral or anal sex after knowing the HIV status of sexual partners (negative/positive/unknown). Participants who report that they are unwilling to disclose their HIV status to sexual partners will be asked questions about sexual orientation, HIV status, type of sexual partners, HIV testing-related violence, and HIV testing history.

Reminder messages will be sent via WeChat for 3 weeks to ensure the completion of follow-up surveys. Participants will be considered lost to follow-up if they do not complete their survey within 1 month.

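### The design table and sample size rest on T1-T4 only and the primary model gives the pre-kit baseline survey no role, at a modest cost in precision

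*Protocol article*

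**What the plan says.** Table 1 of the protocol article starts its intervention/control grid at the first post-allocation period ("T1: 1-3 months after enrollment"). Group A is in the intervention condition at all four time points, and the online-survey row is marked only at T1 to T4.

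The Sample Size section assumes "an overall growth of 10%, four intervention periods", control proportions of "20.6% and 17.8% for most regular and casual male partners, respectively", "a coefficient of variation of 0.40 (usually between 0.15 and 0.40") and "a two-sided α of 0.05, and 90% power". It arrives at 620 and 560 men, and then at 200 per group after allowing for 20% loss.

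Under Study Setting and Recruitment there are five surveys, baseline plus four follow-ups. Baseline comes first and also screens for eligibility. Under Study Measures and Outcomes, baseline records "knowledge of sexual partners’ HIV status during the past 3 months", and the follow-ups build on those behaviour items. Among the follow-up data the same section adds that "the rate of HIV status disclosure by sexual partners will be collected".

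The Analysis Plan makes self-reported disclosure by partners over the past 3 months the primary outcome. Of the generalized linear mixed model it says "Intervention status and time will be treated as fixed effects", with random effects for group and individual. It names no survey rounds.

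**The concern.** Every man answers a question close to the primary outcome before any kits are sent, so a measurement under the control condition exists for all 800 men. The design as drawn does not count it. Without it, the men in Group A are never observed under control and contribute only between-man information on the effect. Only 6 of the 16 group-periods are control; with a baseline period it would be 10 of 20. Chance differences between groups at entry are also left in the estimate instead of being partly removed. What is at stake is a wider confidence interval than the collected data allow.

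**Working it through.** **Inputs.** From the Sample Size section: p0 = 0.206 or 0.178; increase 0.10, read as absolute (a relative 10% would need more than 12,000 men); CV 0.40; two-sided α 0.05; power 90%. From Table 1: four groups and a staircase over T = 4 periods. Adding baseline means an extra all-control column, T = 5. The within-man correlation ρ is not given and is assumed to lie between 0 and 0.8.

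**Formula.** Stepped-wedge variance with fixed period effects and a random group effect (Hussey-Hughes). For four groups:

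Var = 4·s·(s + T·t) / (A·s + B·t)

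Here s = p̄(1−p̄)/n, with p̄ the mean of the two proportions and n the men per group; t = (0.40·p0)². For this staircase A = 10 in both layouts, B = 20 for T = 4 and B = 30 for T = 5. For 90% power, Var must not exceed 0.10²/(1.960 + 1.282)² = 0.01/10.507 = 0.000952.

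**Reproducing the plan, T = 4.**
- Regular partners: p̄ = 0.256, t = 0.0824² = 0.006790. With n = 154, s = 0.190464/154 = 0.0012368. Var = 4 × 0.0012368 × 0.028396 / 0.148163 = 0.000948. Total N = 4 × 154 = 616 (stated 620).
- Casual partners: p̄ = 0.228, t = 0.0712² = 0.005069. With n = 140, s = 0.176016/140 = 0.0012573. Var = 4 × 0.0012573 × 0.021535 / 0.113962 = 0.000950. Total N = 560 (stated 560).

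**With baseline, T = 5.** The limit is met at n = 130 (Var 0.000951, N = 520) and n = 119 (Var 0.000951, N = 476). The falls are 96/616 = 15.6% and 84/560 = 15.0%.

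Twelve choices of variance and between-group SD were tried for each layout, with a 3% tolerance. Five of the four-period versions match both stated figures; none of the five-period versions does.

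**Gain with no group variance.** Men are randomized individually, so true group variance is doubtful. The same formula then applies with s proportional to 1−ρ and t proportional to ρ, and the variance ratio, with baseline to without, is

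(1+4ρ)(1+ρ) / [(1+2ρ)(1+3ρ)]

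| ρ | ratio | variance cut |
|---|---|---|
| 0 | 1.000 | 0% |
| 0.2 | 2.16/2.24 = 0.964 | 4% |
| 0.4 | 3.64/3.96 = 0.919 | 8% |
| 0.6 | 5.44/6.16 = 0.883 | 12% |
| 0.8 | 7.56/8.84 = 0.855 | 14% |

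**Gain under CV 0.40.** With ρ from 0 to 0.8 and 140 to 200 men per group, the cut is about 15-16% throughout.

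**Power.** 20% loss from 200 leaves 160 per group. For regular partners with CV 0.40 and ρ = 0, power is 91% without baseline and 95% with it. With no group variance and ρ = 0.2 it is 99.3% and 99.5%.

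All of this uses a linear approximation to the binary mixed model.

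**The case against.** The strongest reply is that the Analysis Plan does not exclude baseline. A reader might infer that the primary analysis is fixed to T1-T4, but its wording would also fit a model with baseline as a control period. An article may leave the list of rounds to a fuller document. Table 1 also omits a baseline survey that certainly takes place, so its omission there cannot prove exclusion from the model. Sizing the trial on four periods is merely conservative. This stands: T1-T4 is an inference from the table and the sample size, and the point must not be put as a stated restriction.

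A reader might also infer that the lack of a control period in Group A biases the estimate or leaves the trial underpowered. The documents do not support that. Men are randomized 1:1:1:1, the staggered starts identify the effect within T1-T4, entry differences are chance imbalance already reflected in the standard error, and 90% power is met either way.

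Finally, knowing a partner's status is not the same as being told it by him. If the two items differ, baseline does not measure the primary outcome and cannot serve as an outcome period. That also stands and shapes the fix. It does not remove the point, because a related pre-kit measure can still be used as a covariate.

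**Conclusion.** The point holds as one about precision. The design table and the sample size are built on T1-T4, and the model description gives no role to a pre-kit measurement that the trial collects from every man. The cost of leaving it out lies between nothing (ρ = 0, no group variance) and about 15-16% of the variance (CV 0.40). Individual randomization makes the no-group-variance figures, 0% to 14%, the more plausible range. At the planned 10-point effect this hardly changes power; it matters more for the width of the interval, or if the effect is smaller than planned.

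The estimates rest on an assumed ρ, on the linear approximation and, for the all-control-period version, on the baseline and follow-up items being the same. It might seem to follow that the primary outcome should become knowledge of partners' status, since baseline records that and the hypothesis speaks of awareness. That does not follow. The trial is unblinded and the Results section reports the intervention as complete, so replacing the stated outcome would be a larger step than a precision gain justifies.

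**What to change.** Keep disclosure by sexual partners as the primary outcome, and state in the Analysis Plan how baseline is used:

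- Compare the wording of the baseline and follow-up items. If they are the same, enter baseline in the mixed model as an all-control period T0 with categorical time, and add a baseline column to Table 1.
- If they differ, keep T1-T4 as the outcome periods and adjust for baseline partner-status knowledge as a covariate. The gain then depends on how strongly that item correlates with later disclosure.
- Do not use baseline as an outcome period in the HIV-testing-frequency models. The inclusion criteria require no HIV test in the past 3 months, so the baseline count is zero by selection.

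The cost is a check of the questionnaire, a sentence or two in the Analysis Plan and, where the items match, one column in the table. The data are already collected and the sample size need not change.

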### Study Setting and Recruitment

An online cohort will be established. All information, including surveys and HIVST results, will be collected through Gold Data, an online platform dedicated to data collection [32]. A few personal WeChat (Tencent) public accounts that are active in the MSM social circle will release an advertisement to invite MSM to participate in the trial. The advertisement will explain the study objectives, content, and procedures. Restrictions on the use of Internet Protocol addresses will ensure that all participants can complete the survey only once. A 20 RMB (2.84 USD) incentive will be delivered to each participant for the first baseline, and 20 RMB (2.84 USD) for each follow up. Participants who complete all five surveys (baseline and four follow-ups) will earn an extra 200 RMB (28.39 USD) to compensate for their time.

A baseline survey will be used to assess eligibility. Eligible men will be randomly divided into four groups at a ratio of 1:1:1:1. Intervention for the four groups will be randomized and initiated at 3-month intervals. Participants who reach the intervention period will be provided with 2-4 free HIVST kits. The trial will last for 1 year. All individuals who enroll in the trial will be required to complete four follow-up surveys every 3 months. The trial will not be blinded because researchers will be aware of the assignment and sequence with which intervention materials are delivered to each participant. A flowchart describing the trial design is presented in Table 1.

**Table 1 table1:** Study schedule.

Timepoint		Enrollment		Allocation		Post allocation						
**Enrollment**		Aug 2018-Feb 2019		Aug 2018-Feb 2019		T1^a^		T2^b^	T3^c^		T4^d^	
	Online recruitment		X									
	Eligibility screen		X									
	Informed consent		X									
	Allocation				X							

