### Randomization and Allocation

The Mersenne Twister pseudo-random number generator will generate 200 groups of 1-4 random number tables using SAS (SAS Institute) to determine each participant’s group assignment. Then, researchers will randomly select four balls marked 1, 2, 3, and 4 from a closed container to determine the intervention sequence (A-B-C-D). Interventions will be initiated at 3-month intervals.

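### The primary model includes a random effect for four groups formed by individual randomisation; its variance is zero by design, and the term costs a little precision for no benefit

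*Protocol article*

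**What the plan says.** All places are in the protocol article.

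- **Allocation.** Study Setting and Recruitment: "Eligible men will be randomly divided into four groups at a ratio of 1:1:1:1". Randomization and Allocation: the random number generator "will generate 200 groups of 1-4 random number tables using SAS (SAS Institute) to determine each participant’s group assignment". After that, "Then, researchers will randomly select four balls marked 1, 2, 3, and 4 from a closed container to determine the intervention sequence".
- **What a group is.** No site, provider or community defines a group. Men are recruited online, and kits are posted to each man (Intervention Implementation). Contamination Control also makes a man ineligible if a partner or friend is already in the study.
- **Primary model.** Analysis Plan: a generalized linear mixed model in which "Intervention status and time will be treated as fixed effects", and "group clusters and individuals will be estimated as random effects". The Abstract likewise speaks of a group cluster starting the intervention.
- **Sample size.** The Sample Size section uses a stepped wedge calculation with a coefficient of variation of 0.40 and reports totals of 620 and 560 before loss to follow-up.

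**The concern.** A random effect for clusters belongs in a stepped wedge model when pre-existing units, such as clinics or towns, are randomised to start times. Men within such a unit resemble each other before anything is done to them. Here men are randomised one by one to a group, and the groups are then put in order. The net effect is individual randomisation to four start times. Any difference between the groups before treatment is chance, and the person-level variance already covers it. The correlation that does exist, between repeated surveys of the same man, is handled by the individual random effect already in the model.

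The group term therefore has nothing to estimate, and only four units to estimate it from. When chance pushes the estimate above zero, the model gives less weight to the concurrent comparison between groups, which randomisation protects. What is at stake is precision.

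**Working it through.** **Step 1. How the plan treats the groups.** Inputs from the Sample Size section: control proportions "were 20.6% and 17.8% for most regular and casual male partners, respectively", "an overall growth of 10%, four intervention periods", coefficient of variation (CV) 0.40, two-sided alpha 0.05, power 90%. The treatment pattern is that of Table 1, with group A treated from T1.

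Hussey and Hughes variance for I clusters and T periods:

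Var = I·σ²(σ² + Tτ²) / [(IU − W)σ² + (U² + ITU − TW − IV)τ²]

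With I = T = 4, Table 1 gives U = 10, W = 1 + 4 + 9 + 16 = 30 and V = 16 + 9 + 4 + 1 = 30. Hence IU − W = 10, and U² + ITU − TW − IV = 100 + 160 − 120 − 120 = 20.

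Take an absolute rise of 10 points, σ² = p̄(1 − p̄)/n with p̄ the mean of the two proportions, and τ = 0.40 × the proportion.

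| Control proportion | Computed total, CV 0.40 | Stated total | Same formula, τ = 0 |
|---|---|---|---|
| 20.6% | 616-624 | 620 | 324 |
| 17.8% | 560-572 | 560 | 296 |

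The range comes from applying the CV to the control proportion or to the mean proportion. The stated totals are reproduced, so the plan did size the trial as if the four randomised groups were natural clusters. The formula treats repeat surveys of one man as independent, so 324 and 296 only show what the CV contributes; they are not proposed sample sizes.

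**Step 2. Standard error without a group term.** The article gives no within-man correlation ρ, so a range is assumed. With n = 200 × 0.8 = 160 men per group and s² = 0.256 × 0.744 = 0.190464, set σ² = s²(1 − ρ)/n and τ² = ρs²/n.

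For ρ = 0.2: s²/n = 0.0011904, σ² = 0.00095232, τ² = 0.00023808. Then Var = 4 × 0.00095232 × 0.00190464 / (0.0095232 + 0.0047616) = 0.000508, and SE = 0.0225. The same calculation gives 0.0218, 0.0212 and 0.0183 at ρ = 0, 0.4 and 0.6.

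**Step 3. Effect of adding an estimated group variance.** Trials were simulated with the Table 1 pattern, 160 men per group and a true group variance of 0. The group variance was estimated by REML on group-period means, with the within-group covariance taken as known (20,000 trials per setting).

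- The group variance was estimated above zero in 38-39% of trials. In the rest it was exactly zero, and the fit is the same as without the term.
- Variance of the intervention effect, averaged over all trials:

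| Within-man correlation (assumed) | 0 | 0.2 | 0.4 | 0.6 |
|---|---|---|---|---|
| Increase in variance | 12% | 7% | 4% | 2.5% |

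- In the trials with a positive estimate, the increase was about 30%, 17%, 10% and 6% at the same correlations.

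**Step 4. Validity and power.** From a further run of 4,000 trials per setting, with versus without the group term:

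| Correlation | 0 | 0.2 | 0.4 | 0.6 |
|---|---|---|---|---|
| Type I error, with | 0.048 | 0.056 | 0.055 | 0.050 |
| Type I error, without | 0.047 | 0.055 | 0.057 | 0.049 |
| Power for +10 points, with | 0.988 | 0.990 | 0.995 | 1.000 |
| Power for +10 points, without | 0.994 | 0.994 | 0.996 | 1.000 |

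The largest fall in power is 0.994 − 0.988 = 0.006, or 0.6 points.

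**The case against.** The strongest defence is that the term is harmless. In about 60% of trials the variance is estimated at zero and nothing changes; type I error stays near 5%; and power is close to 99% or higher with or without it. The 12% figure also needs repeat answers from one man to be independent, which is implausible. All of this stands, and it limits the weight of the point. It does not supply a reason for the term.

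Three stronger readings are tempting, and the documents support none of them.

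- **That the model discards the randomised between-group comparison.** A random effect down-weights that comparison only as far as its estimated variance exceeds zero. Fixed group effects would remove it, but the plan does not use them.
- **That the estimate becomes a before-after comparison, or that inference is invalid.** Time is a fixed effect, so change within men is still set against concurrent change in groups that have not yet switched. The simulations show no distortion of type I error.
- **That the loss should be computed with the group variance at the planning CV of 0.40.** That would suggest a much larger loss, but it contradicts the premise that the true variance is zero. The Analysis Plan estimates the variance from the data; it does not import the planning value. The CV corresponds to a group SD of 0.40 × 0.206 = 0.0824, which the estimate almost never reached. The median positive estimate was 0.015-0.022.

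**Conclusion.** The point holds as a minor one. The random effect for groups has no basis in the allocation described in the same article: its variance is zero by design and would be estimated from four units. The expected cost is a rise in the variance of the intervention effect of about 2.5% to 7% at within-man correlations from 0.6 to 0.2, reaching 12% only at zero correlation. Power falls by less than 1 point, and there is no bias or inflation of type I error.

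Assumptions: the within-man correlation is not in the article and was varied; the group effect is read as a random intercept; 160 men per group remain after the planned 20% loss; and the simulation is a linear approximation on group means, not the generalized linear mixed model itself.

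The CV of 0.40 rests on the same treatment of randomised groups as clusters. It roughly doubles the total that the stated formula gives, which is conservative for power but has no explanation in the design.

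**What to change.** 1. **Analysis Plan:** remove the random effect for groups. Keep intervention status and time as fixed effects and a random intercept for the individual.
2. **Abstract and Methods:** describe the trial as individually randomised to four start times, and drop the cluster wording.
3. **Sample Size:** justify the between-cluster CV of 0.40 for groups formed by individual randomisation, or remove it.

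The cost is a few phrases. No data, survey or allocation changes. The Results section says recruitment is complete, so item 3 corrects the rationale and does not change the number enrolled. The change to the model should be recorded as an amendment before the outcome data are analysed.

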### Intervention Implementation

When MSM participants reach the intervention period, researchers will send a Quick Response (QR) barcode to each participant to request delivery of 2-4 HIVST kits. The survey is nationwide, and participants will be asked to provide their telephone number and address for delivery of the requested kits.

The HIVST kits will be sent 1-2 days after request and can be used for HIV testing by the participants themselves and their sexual partners. To confirm that participants have used their HIVST kits and help researchers provide consultations, photographs of all HIVST results must be uploaded and submitted through the online survey platform within 20 min after testing. If participants have shared the HIVST kits with their sexual partners, the latter will also be asked to upload a photograph of their HIVST results and complete a questionnaire. The telephone number of participants who share the HIVST kits will also be required for indemnification matching. Participants will be permitted to apply for repeat delivery of 2-4 HIVST kits if previously delivered kits have been used, with no restrictions on the number of HIVST kits permitted during the research period. For participants’ convenience and privacy, the HIVST kits will be delivered by express mail in discreet packaging without visible text mentioning HIVST. Participants will not have to pay for HIVST kits or postage.

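### The logistic regression of condom use on partner HIVST result carries no stated allowance for within-man correlation, although a man can contribute several surveys and partners

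*Protocol article*

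**What the plan says.** The Analysis Plan names its methods in sequence.

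- **Primary outcome:** generalized linear mixed models with intervention status and time as fixed effects, "whereas group clusters and individuals will be estimated as random effects".
- **Other secondary outcomes:** "Similar methods will be used to measure secondary outcomes, including the frequency of HIV testing uptake, frequency of syphilis testing", a list that goes on to number of partners and unprotected sex.
- **Partner result and condom use:** introduced as an addition to those, "logistic regression analysis will be used to explore the relationship between the HIVST results of sexual partners and condom use during sexual intercourse". No random effect, GEE, robust variance or unit of analysis accompanies it.

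Other sections show how many records one man can supply.

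- **Surveys** (Study Measures and Outcomes): "Follow-up surveys will be performed at 3, 6, 9, and 12 months after enrollment". Condom use is asked according to what the man knows of the partner's status.
- **Kits** (Study Setting and Recruitment): "Participants who reach the intervention period will be provided with 2-4 free HIVST kits". Intervention Implementation allows further requests once kits are used, "with no restrictions on the number of HIVST kits permitted during the research period".
- **Partner results** (Intervention Implementation): each partner who receives a kit is asked to upload a photograph of the result and fill in a questionnaire.
- **Intervention periods** (Table 1): groups A, B, C and D have 4, 3, 2 and 1 follow-up periods in the intervention condition.

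**The concern.** The plan recognises repeated measurement on individuals for the primary outcome. It then names a different method, with no individual effect, for an analysis whose data have the same repeated structure and may have several partners per man as well. Logistic regression in its standard form takes the records as independent. A man's condom use is likely to be similar from one survey or partner to the next, and his partners' results may be similar too, for instance when the same regular partner tests more than once. When both hold, the standard error for the partner-result effect is too small and P<.05 is reached too often.

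The analysis bears on secondary aim (i), the change in sexual behaviour after a partner's status is disclosed. It is the only analysis named in the plan that links a partner's test result to condom use. An association declared on too narrow an interval could be read as evidence that knowing the result changes behaviour.

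**Working it through.** The documents give no figure for this analysis, so there is none to reproduce. They also give no within-man correlation and no expected number of partner results per man. The correlations below are therefore assumptions, shown as a range.

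**Step 1. Records per man.** Partner results from study kits arise only in intervention periods. Take one record per intervention-period survey and equal groups (200 men each in the Sample Size section). Groups A to D then supply 4, 3, 2 and 1 records per man. The effective number is

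m = Σm² / Σm = (16 + 9 + 4 + 1) / (4 + 3 + 2 + 1) = 30 / 10 = 3.

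**Step 2. Design effect.** For a covariate that may vary within a man,

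DE = 1 + (m − 1) × ICC_y × ICC_x,

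where ICC_y is the within-man correlation of condom use and ICC_x that of partner result. The true error of a nominal two-sided 5% test that ignores clustering is 2 × [1 − Φ(1.96 / √DE)].

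**Step 3. Results at m = 3.** The last column is 1 − 1/√DE.

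| ICC_y | ICC_x | DE | True error | SE understated by |
|---|---|---|---|---|
| any | 0 | 1.0 | 5% | 0% |
| 0.1 | 0.5 | 1.1 | 6% | 5% |
| 0.1 | 1.0 | 1.2 | 7% | 9% |
| 0.3 | 0.5 | 1.3 | 9% | 12% |
| 0.3 | 1.0 | 1.6 | 12% | 21% |
| 0.5 | 0.5 | 1.5 | 11% | 18% |
| 0.5 | 1.0 | 2.0 | 17% | 29% |

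With one record per man, m = 1, so DE = 1 and the error is 5% whatever the correlations.

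**Step 4. Simulation check.** There were 300 men and 600 replicates, with no true association. Random intercepts of SD 1.8 on the logit scale were given to condom use, and to partner result where it was clustered.

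| Records per man | Partner result clustered | Independence assumed | Cluster-robust |
|---|---|---|---|
| 1 | yes | 5.2% | 5.2% |
| 2 | yes | 5.2% | 3.7% |
| 4 | yes | 8.5% | 3.8% |
| 4 | no | 6.0% | 6.3% |

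The Monte Carlo standard error near 5% is √(0.05 × 0.95 / 600) = 0.9 percentage points. Only the 8.5% stands clearly above nominal. The simulation supports the direction and the condition: inflation needs several records per man and clustering of both variables. At two records it is too small to detect here.

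**The case against.** The strongest objection is that the article never says records will be pooled as independent. It names logistic regression and no more. That label can cover a random intercept, GEE or an analysis of one record per man, and a condensed article may leave such detail to the full plan. This stands in part. A reader might infer that the plan commits to treating correlated records as independent, and the text does not support that. What remains is that the article does state a method, sets it apart from mixed models it has just described with an individual effect, and attaches no allowance for correlation. Applied as written to several records per man, that method would ignore it.

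Three further inferences are tempting and should not be drawn.

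- **An error of 12% to 19%.** A design effect of 1.6 to 2.2 (four records, correlation 0.2 to 0.4) gives this range, but only if every man supplies four records and the covariate is constant within him. Partner results arise only in intervention periods, so group D has one such survey, and they can differ between partners. Several partners per survey would raise m, but a result that varies among a man's partners pulls the inflation back down.
- **Loss of the ordinal condom scale.** The item has four levels (never to always), but nothing says they will be dichotomised, and logistic regression includes cumulative-logit models.
- **The same fault in the disclosure-factor analysis.** That sentence lists factors to be examined and names no method, so there is nothing to correct.

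It is also true that the stated purpose is to explore, that the sentence promising 95% confidence intervals concerns intervention effects, and that unprotected sex, compared between conditions, already falls under the mixed-model approach.

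**Conclusion.** The point holds in a conditional form. The article names logistic regression for partner result and condom use, separately from the mixed models, with no allowance for within-man correlation in data that can contain several records per man. If those records are analysed together by that method, intervals are too narrow whenever partner result clusters within man. With an effective 3 records per man, nominal 5% error becomes about 6% to 17% for assumed ICC_y of 0.1 to 0.5 and ICC_x of 0.5 to 1.0. It remains 5% if each man gives one record or the covariate does not cluster.

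The size therefore rests on correlations that the documents do not give and on one record per intervention-period survey. The consequence is confined to one exploratory secondary analysis, and the primary analysis is unaffected. It is a weakness worth correcting, not a demonstrated error in a reported interval.

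**What to change.** In the Analysis Plan, state the unit of analysis for this regression. Fit it as logistic regression with a participant random intercept, consistent with the primary model, or by GEE clustered on participant with robust variance. Clustering on the participant covers both repeated surveys and several partners of the same man. Name which of the two is used, because the first gives a within-participant odds ratio and the second a population-averaged one.

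Report the result as a non-randomised association. Partner result is not allocated, and it is known only for partners who were offered a kit and used it.

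The cost is one or two sentences, with no new data and no change to the primary analysis. The only downside is slightly wider intervals.
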